#### Influenza like-illness (ILI) case definition

ILI symptoms are based upon case definitions of influenza issued by NSW Health and Centers for Disease Control and Prevention (CDC) as of 26 March 2010 [16,17]. Febrile upper respiratory tract illnesses occurring during the peak influenza period was identified as the most specific clinical case definition expected to have the highest positive predictive value for true influenza [18].

### Data collection

Four methods will be used to collect data about participants during the study:

*Surveys*: Questions are informed by studies tracking ILI symptoms in the Australian community [19,20], and studies investigating influenza experiences and attitudes amongst university students and healthy working adults [14,21-26]. The following surveys will be conducted:

• Pre-study survey to obtain participant demographics and health status at study registration.

• Monthly one-minute follow-up surveys to obtain participant self-reported symptoms of ILI, use of health services, and impact on work and study due to ILI symptoms throughout the study.

• Post-study survey to obtain participant influenza vaccination status. For those who receive *Healthy.me *intervention, they will be asked in addition for their perceived usefulness of *Healthy.me*.

*System logs*: During the study, participant actions on *Healthy.me *will be unobtrusively logged.

*Personal health data*: Data entered by participants into *Healthy.me *about their health (e.g., medications used, scheduled tasks and appointments, members in healthcare team).

*Clinical audit*: This will be conducted post-study for patients at the University Health Service (UHS), to validate self-reports of vaccination and visits to a healthcare professional related to ILI symptoms for a subset of participants before and during the study. Clinical audits will be conducted on site at the UHS, linking UHS patient records with our survey data using exact matches on participants' surname, date of birth, and an approximate match on first-name. Extracted records will be replaced with a de-identified ID, and all names will be removed prior to analysis.

### Analysis plan

Statistical significance is defined a priori as a P value of less than 0.05 (determined using a two-tailed test). Data will be collected by online survey software KeySurvey [27] and analysed using PASW Statistics 18 [28].

#### Baseline comparisons

Comparisons of baseline variables between PCHMS and waitlist groups will be conducted using Student's t-tests for continuous variables and χ^2 ^tests for categorical variables, to assess whether randomisation was performed properly. Adjustment for baseline characteristics is planned to correct for possible imbalance between the randomised groups and to provide a stratified estimate of the effect of intervention if applied [29,30].

#### Primary analysis

Differences in proportions of participants obtaining influenza vaccination during the study will be compared between waitlist and PCHMS groups. All intervention recipients who had the opportunity to use the PCHMS but did not do so will be included in the primary analysis. Differences in participant proportions between waitlist and PCHMS groups will be analysed using χ^2 ^test. Proportions will be reported with 95% confidence intervals.

Adjustments for baseline characteristics and potential confounders will be made through the use of sequential logistic regression [31]. Baseline characteristics (Table 1), and factors that may affect influenza vaccination collected at post study (i.e. contact with children during study, past history of influenza vaccine) will be entered at Step 1 of the regression; and group allocation (PCHMS vs. waitlist) will be entered at Step 2.

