## Methods/Design

### Study design

A randomised controlled trial with a two-group parallel design (with intervention allocation ratio 1:1) is used to evaluate the efficacy of *Healthy.me*, reported in accordance to the 2010 CONSORT statements (Figure 1) [5]:

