### Sample size considerations

The sampling unit is the participant and the unit of analysis is also the participant. A conservative estimate of 600 participants with 300 in each group is needed to detect a 10% difference in influenza vaccination rate between the control group (15%) and the intervention group (25%). This estimate is calculated at 5% level of significance, 80% power (two-sided test), with an anticipated participant dropout rate around 10% [12].

The effect size estimate is based on a review assessing the effectiveness of patient reminder systems in improving immunization rates, which can range from 5 to 20% [13]. The baseline rate estimate of influenza vaccination was informed by our audit conducted at the University Health Service, showing 16% of patients at the practice received FluVax or PanVax between 5/3/2009 to 5/11/2009. This estimate is also supported by literature reporting 18 to 30% of university students and healthy adults (18 to 49 years old) obtaining influenza vaccination in a year [14,15].

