• *Social influence and access to Healthy.me*: The social networks of individual participants may span the intervention and control arms of this study, and see intervention subjects un-blind control subjects with information obtained from the intervention. As this is a pragmatic trial in the real world, such effects cannot be controlled for. Indeed participants' social networks are likely to influence access to Healthy.me if the intervention was in routine use. We will attempt to measure this effect by asking participants in the control arm if they have been in contact with intervention arm subjects. If a significant group is identified, we will conduct separate analyses to estimate the impact of any such effect on overall trial results.

• *Baseline comparisons*: As this is a pragmatic trial of a multifaceted intervention in a complex environment, it is possible that baseline variables associated with subjects might also influence the outcome. For example, having a prior history of obtaining influenza vaccination may predict future vaccination rates, independently of any additional intervention. We will identify potential baseline variables that might influence outcome, including gender, and test for unequal distribution of these variables in the intervention and control populations. Should there be a significant difference in their distribution due to chance bias, these will be fitted in an analysis of covariance to model their impact on any observed differences between the two arms [39].

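### The adjusted logistic model conditions on two covariates collected at study end, so its group effect can be biased in either direction; the chi-square test is unaffected

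*Protocol article*

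**What the plan says.** All references are to the protocol article.

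- **Primary analysis, first paragraph.** The main comparison is unadjusted: "Differences in participant proportions between waitlist and PCHMS groups will be analysed using" a chi-square test, with 95% confidence intervals for the proportions.
- **Primary analysis, second paragraph.** A sequential logistic regression follows. Step 1 takes baseline characteristics together with "factors that may affect influenza vaccination collected at post study (i.e. contact with children during study, past history of influenza vaccine"). Group allocation enters at Step 2, so the group effect is conditional on everything in Step 1.
- **Blinding and assessment.** Participants cannot be completely blinded. They learn their group after consent and the pre-study survey, which is well before the post-study survey.
- **Intervention group and exposure.** The intervention arm receives influenza information, email reminders and indications for vaccination during the study.
- **Limitations, Baseline comparisons.** The example given of a baseline variable that could influence the outcome is that "having a prior history of obtaining influenza vaccination may predict future vaccination rates, independently of any additional intervention".
- **Data collection.** A baseline instrument exists: "Pre-study survey to obtain participant demographics and health status at study registration". The clinical audit at the University Health Service covers the period before as well as during the study, for a subset. Table 3 lists audit data from the previous 12 months under Baseline.
- **Outcome measures.** A participant can enter the primary analysis on the post-study survey, the audit, or both.

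**The concern.** Covariate adjustment in a randomised trial is safe when the covariates are fixed before allocation. Here two are not.

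Contact with children during the study is a post-randomisation variable by definition. Past vaccination is a pre-randomisation fact, but the value used is a self-report at study end. By then one arm has had months of vaccination material, and every respondent knows whether they were vaccinated. What they report can depend on arm, on outcome, or on both. A dose received during the study might also be counted as past history. An arm difference in the recalled variable may then be an effect of the intervention on reporting, and adjusting for it takes something away from, or adds something to, the randomised contrast.

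The article is also at odds with itself. It calls vaccination history a baseline variable in Limitations but collects it at post-study in the analysis plan.

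At stake is the adjusted estimate and its test, which stand under the primary-analysis heading. True baseline history would add precision; history recalled at study end can lose that gain and introduce bias.

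**Working it through.** **1. The plan's own figure.** Inputs from Sample size considerations: 15% against 25%, two-sided 5%, 80% power, about 10% dropout.

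- Uncorrected: n = [1.96·√(2·0.20·0.80) + 0.8416·√(0.15·0.85 + 0.25·0.75)]² / 0.10² = (1.1087 + 0.4724)² / 0.01 ≈ 250 per group.
- With continuity correction: (250/4)·[1 + √(1 + 4/(250·0.10))]² = 62.5·(1 + √1.16)² ≈ 270 per group.
- Dropout: 270/0.9 = 300 per group, 600 in total. This matches "A conservative estimate of 600 participants with 300 in each group".

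The sizing is for two unadjusted proportions and does not involve the covariates in question.

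**2. Timing of each Step 1 item.**

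| Covariate | Fixed before allocation? | Reported before allocation? |
|---|---|---|
| Baseline characteristics (pre-study survey) | yes | yes |
| Past influenza vaccination | yes | no, at post-study |
| Contact with children during study | no | no, at post-study |

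**3. Direction of bias (large-sample logistic fits).** Marginal rates are held at 15% and 25%, so the crude odds ratio is (0.25/0.75)/(0.15/0.85) = 1.89. All covariate inputs are assumptions: prior vaccination in 20–40%, history–outcome odds ratio 3–5.

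| Recorded history | Adjusted group OR |
|---|---|
| Correct | 1.94–2.03 |
| Same error in both arms (sensitivity 90%, specificity 95%) | 1.92–1.99 |
| Intervention arm over-reports, 5% of those without history | 1.84–1.91 |
| As above, 10% | 1.73–1.82 |
| As above, 20% | 1.56–1.72 |
| In-study dose counted as history, 10–50% of those vaccinated without prior history | 1.95–2.11 |

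The last row is a rise of 0.01–0.09 over the correct value. The move from 1.89 to 1.94–2.03 with correct history is non-collapsibility of the odds ratio, not bias.

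For contact with children (30% in controls, association OR 1.5–3), the group OR is 1.90–1.95 when contact is equal in the arms, which is no bias. It is 1.98–2.21 if contact is 20% in the intervention arm and 1.73–1.82 if it is 40%.

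**4. Size of the error in the test (simulation, 2,000 trials, 270 per arm).** Model: logit P = −2.6 + 1.8·history + b·arm, with history in 30%. The values b = 0 and b = 0.75 give rates of about 14% in controls and 24% under the effect. All reporting errors are assumed.

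| Error in recalled history (control / intervention) | Power at b = 0.75 | Rejection at b = 0 |
|---|---|---|
| None (true history) | 88–89% | about 5% |
| Equal in both arms | 87% | 4.5% |
| Forgotten 15% / 10%; falsely reported 2% / 4% | 82% | 5.8% |
| Falsely reported 0 / 5% | 82% | 5.6% |
| Forgotten 10% / 5%; falsely reported 0 / 3% | 80% | 6.2% |
| Forgotten 10% / 5%; falsely reported 0 / 5% | 77% | 7% |
| Forgotten 20% / 5% only | 78% | 6.8% |
| Falsely reported 0 / 10% only | 72% | 8.5% |
| Forgotten 20% / 5% and falsely reported 0 / 10% | 58–59% | 13% |

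The unadjusted comparison has 84–85% power throughout. In the last row the mean log odds ratio falls from 0.75 to 0.52, that is from e^0.75 = 2.12 to e^0.52 = 1.68.

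**5. Who is in the adjusted model.** A participant whose outcome comes only from the audit has no post-study survey and so no value for contact with children. In a complete-case fit that person drops out, and the adjusted and unadjusted results describe different people. Vaccination history may still be available for that person from the previous-12-month audit.

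**The case against.** The case against a stronger reading is substantial, and most of it stands.

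- **A reader might infer that the primary result is compromised.** The document does not support that. The chi-square test comes first, the trial is sized on it, and it uses none of these covariates.
- **A reader might take the 13% rejection rate as the expected error.** It comes from two assumed differential errors stacked in the same direction. Taken singly or made milder, they give about 6% to 8.5%, and equal error gives no inflation. Limitations also argues that self-reported vaccination status is acceptably accurate. That argument concerns overall accuracy, however, and does not exclude a difference between arms.
- **A reader might give both covariates equal weight.** Nothing in the article suggests that a vaccination website changes contact with children, and with equal contact there is no bias. That half is a matter of principle more than of likely size.
- **A reader might conclude that audit-only participants have neither covariate.** That is wrong: the audit reaches back 12 months and can supply vaccination records for linked participants.
- **Asking earlier has a price.** Under Recruitment strategy, the advertising deliberately does not reveal that influenza vaccination is the topic. A pre-study vaccination question might hint at it and prompt controls. The article does not give this as the reason for post-study collection, but the tension is real. Any prompting would fall equally on both arms.

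What the objection does not remove is that Step 1, as written, includes values reported after allocation, exposure and outcome, and that it treats as a post-study item what Limitations calls a baseline variable.

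**Conclusion.** The point holds for the adjusted analysis only. Bias in the adjusted group effect is possible, not certain, and its direction cannot be predicted. Over-reporting of history in the intervention arm lowers the odds ratio, while counting the in-study dose as history raises it slightly. It therefore cannot be called conservative.

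Under the assumed errors, the adjusted test rejects a true null in about 5% to 13% of trials, with most differential scenarios between about 6% and 8.5%, and its power lies between about 87% and 58%. In every differential scenario tried, adjusting for recalled history gave less power than no adjustment, whereas true baseline history gave more. These figures rest on assumed prevalence, association and reporting errors, because the article supplies none.

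This should be corrected before the adjusted model is used, but it does not call the chi-square comparison or the sample size into question.

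**What to change.** 1. Restrict Step 1 of the main adjusted model to values fixed and recorded before allocation.
2. Move any model containing covariates collected at post-study, including contact with children during the study, to a sensitivity analysis labelled as such.
3. If vaccination history is wanted as a covariate, obtain it from an item in the pre-study survey, placed among other health questions. Use the previous-12-month audit to check it in linked participants.
4. Align the Primary analysis text with Limitations, so that vaccination history is a baseline variable in both.

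**Cost.** One survey item and a few lines of analysis text; the sample size and the chi-square test do not change. The downside is that a pre-study vaccination question may hint at the study topic, equally in both arms. If that is unacceptable, omit history from the main adjusted model and accept the loss of the small precision gain (88–89% against 84–85% power in the assumed model).

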#### Secondary and ancillary analyses

Differences in proportions of participants between different groups (e.g. waiting list vs. PCHMS; used PCHMS once vs. used PCHMS more than once) will be examined using χ^2 ^test for each of the following activities experienced at least once during the study: i) visited the University Health Service (or a healthcare professional); ii) used medications or remedy; and iii) experienced performance impairment. Differences in average number of days of absence per participant will be compared between waitlist and PCHMS groups using Student's t-test. Reasons for receiving (or not receiving) influenza vaccine and impact of ILI symptoms will be reported using descriptive statistics.

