**Figure 2 F2:**
[figure not shown]
**Features of *Healthy.me *(^© ^University of New South Wales, 2009-2012)**.

1. Personal Record: Allows for self-recording of medical test results and health measurements (not available to participants in this study).

2. Pillbox: Allows for self-recording of current medications and medication adherence.

3. Schedule, to-do list and reminders: An online schedule to self-record and keep track of health-related appointments, to-do items, which sends email reminders.

4. Team: A feature that allows the self-recording of clinical and non-clinical personnel looking after one's health.

5. Journeys: Consumer-specific care pathways that provide knowledge in an actionable way. A feature that describes the different stages in the management of health conditions that can be used to personalise other PHR sections in the system, and provides advice on what to expect and how to prepare for each stage. (Participants in this study had access to an influenza vaccine journey).

6. Social features for this study included: (i) a profile for each member to store and customise their personal information, (ii) the ability to send and receive messages with other members on *Healthy.me*.

Studies suggest that by addressing both knowledge-based (e.g. lack of awareness) and system-based (e.g. inconvenience) barriers in accessing health services, patients and consumers are more likely to uptake preventative health measures, such as influenza vaccination [6]. Our PCHMS is designed to address both knowledge-based and system-based barriers faced by consumers when accessing and utilising health services.

The PCHMS thus integrates a number of tools to address knowledge and system barriers that influence consumers' engagement with health services. Our PCHMS contains a PHR, as well as online social networking mechanisms that allow participants to interact with healthcare professionals at the service provider and other consumers, and additional tools to support consumer decision making and subsequent task management. In addition, it is integrated with consumer-specific care pathways (called "journeys") that provide knowledge in an actionable way. For example, at the point that a consumer encounters advice to seek influenza vaccination, they are immediately able to book an appointment with a medical practitioner, or set themselves a reminder.

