#### Intervention group and exposure

The period of access to *Healthy.me *will vary depending on the date of participant registration. During the study *Healthy.me *will provide participants in the intervention group with information and forward email reminders about influenza, indications for vaccination, as well as an email link to the University Health Service for participants to book an appointment for influenza vaccination or other medical concerns, should they wish to use that service (Figure 4).

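### The unadjusted once-versus-more-than-once use comparison is biased towards an apparent dose-response, by an amount the protocol article does not let us fix

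*Protocol article*

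**What the plan says.** The section Secondary and ancillary analyses names two example groupings for the chi-square test: the randomised one (waiting list against PCHMS) and a usage one, "used PCHMS once vs. used PCHMS more than once". Both use the same test "for each of the following activities experienced at least once during the study". The activities are a visit to the University Health Service or a healthcare professional, use of medication or a remedy, and impaired performance. The Analysis plan sets two-sided P < 0.05 without distinguishing the two groupings.

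Three other places bear on the usage grouping:

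- Intervention group and exposure: the period of access "will vary depending on the date of participant registration".
- Study procedure: the monthly surveys run from recruitment to study completion, so survey follow-up shortens together with access.
- Description of intervention: on meeting the vaccination advice, users can act at once, since "they are immediately able to book an appointment with a medical practitioner, or set themselves a reminder". Data collection adds that actions on the system are logged. It does not say whether a booking session, or use after the event, counts as use.

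The planned adjustments lie elsewhere. The sequential logistic regression is for vaccination, and the baseline adjustments address imbalance between the randomised arms.

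**The concern.** The number of times a person uses the system is observed after randomisation, so randomisation does not protect this contrast. Two mechanisms push it in the same direction without any benefit of use:

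- **Access time.** An early registrant has longer both to log in again and to report an event. An at-least-once outcome makes no allowance for person-time. All three outcomes are exposed to this.
- **The outcome helps define the group.** Someone who returns to Healthy.me to book a visit moves from the once group to the more-than-once group because of that visit. This bears mainly on the health service visit outcome.

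Visiting the University Health Service is the only outcome that Table 2 labels secondary, and hypothesis 2 concerns it. A significant usage contrast on that outcome could be read as support for the hypothesis when it reflects follow-up time or reverse causation.

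**Working it through.** **The plan's own figure.** The article gives no figure for this contrast, only the trial size: "A conservative estimate of 600 participants with 300 in each group is needed", for 15% against 25%, two-sided 5%, 80% power and about 10% dropout.

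- n = [1.96·√(2·0.20·0.80) + 0.8416·√(0.15·0.85 + 0.25·0.75)]² / 0.10² = (1.1087 + 0.4724)² / 0.01 ≈ 250 per arm.
- The continuity correction gives 270, and 270 / 0.90 = 300. The stated 600 is reproduced.
- The largest possible number of users is therefore 300 × 0.90 = 270. Never-users reduce it.

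**Access time alone (assumed rates, no effect of use).** Registration spreads evenly over R months, so access T is uniform from 6−R to 6 months. Uses are 1 + Poisson(λT). Visits have constant monthly hazard h and are independent of use given T. With M(r) = [e^(−r(6−R)) − e^(−6r)] / (rR):

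- P(once) = M(λ); P(once and no visit) = M(λ+h); P(no visit) = M(h).

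For λ = 0.20 and h = 0.10:

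- R = 5: M(0.2) = 0.518, M(0.3) = 0.384, M(0.1) = 0.712. Visits are 1 − 0.384/0.518 = 25.9% (once) and 1 − (0.712 − 0.384)/(1 − 0.518) = 31.9% (more than once). The false difference is 6.1 points. The standard error with 270 users is √[0.288·0.712·(1/139.7 + 1/130.3)] = 0.055, so z = 1.10 and the test rejects about 20% of the time.
- R = 3: M(0.2) = 0.413, M(0.3) = 0.268, M(0.1) = 0.640. Visits are 35.0% and 36.7%, a difference of 1.6 points, with about 6% rejection.

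Over log-in rates of 0.15-0.30 and visit rates of 0.08-0.15 per month, rejection is about 5-6% for R of 3 months or less and about 16-32% for R = 5. With visit rates of 0.05-0.10 and log-in rates of 0.1-0.4, R = 5 gives 10-25%.

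**Separate booking sessions alone (equal access, no effect of use).** Assume 25% visit, 40% would be repeat users anyway, and a share q of visitors adds a session in order to book.

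- Visit rate, once = 0.25·0.60·(1−q) / [0.25·0.60·(1−q) + 0.75·0.60].
- Visit rate, more than once = 0.25·(0.40 + 0.60q) / [0.25·(0.40 + 0.60q) + 0.75·0.40].

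| q | Once | More than once | Difference | Rejection, 270 users |
|---|---|---|---|---|
| 5% | 24.1% | 26.4% | 2.3 points | 7% |
| 10% | 23.1% | 27.7% | 4.6 points | 14% |
| 20% | 21.1% | 30.2% | 9.2 points | 41% |

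For q = 20%: SE = √[0.25·0.75·(1/153.9 + 1/116.1)] = 0.053, so z = 1.72 and rejection = Φ(1.72 − 1.96) ≈ 0.41. If extra log-ins instead follow the Poisson model over six months (0.15-0.30 per month), q = 20% gives 11-29%.

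**Fewer users.** With 135 users, z at q = 20% falls to 1.72/√2 = 1.22, so rejection is about 23%. The 5-month access-time rates fall to about 10-17%.

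**Check.** With equal access and no booking sessions counted, simulated rejection is 4.8-5.1%, the nominal level. With either mechanism active, every simulated setting favoured repeat users.

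**The case against.** The strongest reply is that the size rests on invented inputs and that the contrast is a minor one.

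- **Registration spread.** A study from May to October and a wait of about six months for controls fit a short registration period, and at 3 months or less access time hardly matters. This stands as a limit on size. The article says that access varies but not by how much.
- **Booking.** The article describes booking at the moment of reading the advice. A booking made in a person's only session leaves that person in the once group, so only separate sessions matter, and their share is unknown. This stands too.
- **Scope.** Booking does not directly touch medication use or impairment. The Pillbox lets users record medication, so taking one could prompt another log-in, but how often is unknown. If audited visits are counted over the fixed study period rather than from enrolment, the access-time effect weakens for that outcome.
- **Status.** The usage grouping is introduced as an example among secondary and ancillary analyses. Hypothesis 2 has its own randomised comparison of University Health Service visits.

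A reader might infer that the trial will report a spurious dose-response, or that it claims one. Neither is supported. The article calls this contrast neither a dose-response nor causal, and the false-positive rate may be close to 5%. Nor should the example be read as removing never-users from the trial: the primary analysis keeps them.

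What survives is that the usage contrast is one of only two groupings named, its test is stated, both mechanisms follow from the article, and nothing in it corrects them.

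**Conclusion.** The point holds as a bias of known direction and unknown size. As written, the contrast leans towards repeat users with no effect of use: through access time for all three outcomes, and through separate booking sessions mainly for health service visits. The false-positive rate runs from nominal to several times nominal, depending on registration spread, log-in rates and booking share, all of which are assumed here. No single percentage should be quoted as the error rate of this analysis. The primary analysis and the waitlist-versus-PCHMS comparisons are unaffected. The change is worth making because the secondary outcome is among those tested and the remedy is cheap. It is not a flaw in the trial's main conclusions.

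**What to change.** Replace the unadjusted chi-square for this contrast with an analysis that:

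1. classifies use within a fixed window after registration, or before the first event, and states what counts as a use;
2. counts outcomes only after that point;
3. adjusts for follow-up time and baseline covariates;
4. shows never-users as a separate group;
5. is labelled observational.

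At minimum, report the contrast descriptively, without a P value, and state that it is not evidence for hypothesis 2.

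A complier-average estimate with randomisation as the instrument is not a substitute. The intervention group's email reminders can act without any log-in, and a two-arm instrument cannot identify the effect of using the system once rather than more than once.

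The cost is a few lines of analysis text and some programming. Events in the early window are lost from this ancillary analysis.
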